## Abstract

**Background:**

In the United States, poor adherence accounts for up to 70% of all medication-related hospital admissions, resulting in $100 billion in health care costs annually. In pediatrics, adherence is largely dependent on caregivers. In a high-risk hematopoietic stem cell transplant (HSCT) population, caregivers are isolated with their child due to infection risk and must manage challenging treatment regimens at home, often with limited time and support. Complex behavioral interventions, typically employed to address adherence, are difficult to deliver and manage in the context of these daily tasks. The most successful adherence interventions, and thus improved clinical outcomes, have included mobile health (mHealth) reminder approaches and a direct measure of adherence.

**Objective:**

This is a 3-phase project, with this protocol describing phase 2, to determine the usability and feasibility of an mHealth app (BMT4me) designed to promote adherence to immunosuppressant medication and to track symptoms among children who received HSCT.

**Methods:**

This study uses an iterative convergent mixed methods design to develop and assess the usability and feasibility of an adherence digital health intervention. We will recruit 15 caregivers of pediatric patients receiving HSCT to complete user testing. Qualitative and quantitative data will be integrated to enhance and expand upon study findings.

**Results:**

Enrollment began in September 2021 and is ongoing. A total of 7 caregivers have enrolled. We anticipate completion by fall 2022. We anticipate high usability scores and a better understanding of unique features within the app that are needed for HSCT families post transplant. To date, usability scores among enrolled participants are greater than 70%. Feedback from qualitative interviews is being used to further adapt the app by adding specific weekly logs, call provider options, and voice to text.

**Conclusions:**

This protocol describes a mixed methods usability and feasibility study to develop and implement a smartphone app for caregivers of children receiving HSCT. The app was designed to improve immunosuppressant adherence and to track symptoms in the acute phase post discharge. Study findings will inform further refinement of the app and the feasibility of a pilot randomized controlled trial examining efficacy on clinical outcomes.

**Trial Registration:**

ClinicalTrials.gov NCT04976933; https://clinicaltrials.gov/ct2/show/NCT04976933

**International Registered Report Identifier (IRRID):**

DERR1-10.2196/39098

## Introduction

### Background

In the United States, poor adherence accounts for up to 70% of all medication-related hospital admissions [1], resulting in $100 billion in health care costs annually [2]. An estimated 50% to 80% of pediatric patients are nonadherent to medications [3-6]. Reasons for nonadherence are multifactorial. The most important determinants of nonadherence are consistently documented as complexity and duration of treatment regimens, as well as forgetfulness [7-9]. Thus, children undergoing difficult hematopoietic stem cell transplants (HSCTs) who require medication indefinitely are at high risk for medication nonadherence.

HSCT is the transplantation of hematopoietic stem cells derived from bone marrow (ie, “bone marrow transplant” or peripheral blood stem cells). HSCT became the common treatment for life-threatening malignant (eg, leukemia, lymphoma) and nonmalignant (eg, aplastic anemia, sickle cell disease, immune deficiencies) disorders in the mid-1900s. Recipients of bone marrow transplants must adhere to multifaceted outpatient regimens that require strict personal hygiene, environmental restrictions, and complex medication regimens. These include wearing masks, avoiding large crowds, frequent mouth care, and taking multiple time-sensitive medications throughout the day.

Lack of adherence to any of these regimens can be life-threatening [10]. Adherence to immunosuppressant medications during the acute phase (ie, the first 100 days) post transplant is critical to prevent graft versus host disease and avoid graft failure. Studies in children with HSCT report suboptimal adherence rates (52%-78%) that worsen over time [11-13]. Nonadherence to oral medications has been associated with a greater incidence of infections in children during the outpatient HSCT treatment phase [12]. Providers also report adherence as a major concern for outpatient pediatric HSCT recipients [14]. However, no studies have examined adherence specifically to immunosuppressant medications, which are key to engraftment and ultimately survival.

Multiple factors influence adherence, but, ultimately, the final common pathway to adherence is human behavior [15]. For children, caregivers are ultimately responsible for adherence, including refilling prescriptions, retrieving medications, and administering them correctly. In a high-risk HSCT population, caregivers are susceptible to fatigue and stress from being isolated with their child due to infection risk and independently managing complex treatment regimens at home, often with limited time and support. Unfortunately, behavioral interventions employed to address adherence are often difficult to deliver and manage in the context of these daily tasks. Specifically, these interventions can involve 8 to 12 face-to-face sessions, tracking behaviors, practicing skills, and other homework, which can be overwhelming to caregivers.

Alternatively, behavioral economics (BE) theory suggests that small “nudges” can produce and sustain behavior change [16]. A BE approach is a significant paradigm shift from the complex cognitive behavioral theories that inform most adherence interventions. Instead, BE assumes decision-making can be influenced through low-intensity interventions to lead patients to optimal choices [17]. Adherence to medication and exercise programs using BE-designed interventions in adults have some initial promising data [18-21]. Within pediatrics, for example, BE has been successful in increasing fruit consumption and improving vaccination rates [22-24].

With mobile health (mHealth) access nearly ubiquitous and an estimated 250 billion mHealth app downloads in 2022 [25], technology has great potential to improve adherence [26]. mHealth interventions based on BE principles may be ideal, as they provide sophisticated yet simple “nudges” to individuals [27]. Such reminder apps target forgetfulness, a common reason for poor adherence [28,29]. These mHealth interventions are ideally suited for complex HSCT regimens requiring multiple-dose medications that are time sensitive.

A recent systematic review in solid organ transplant reported the most successful interventions, resulting in increased adherence and improved clinical outcomes (eg, complications, hospital admissions, survival) have used mHealth reminders and a direct measure of adherence [30]. Although direct measures of adherence (eg, serum assays) can avoid bias inherent in self- or parent reports, no studies have used direct measures of adherence or mHealth interventions to promote immunosuppression adherence in the acute phase after an HSCT (ie, discharge to day 100). Furthermore, the feasibility, acceptability, and efficacy of BE-designed mHealth interventions have not been examined in the HSCT population. Thus, this study utilizes a BE approach to mHealth app development, as well as an iterative approach of cyclical evaluation and revision, to maximize the usability and adoption of the digital intervention, BMT4me.

### BMT4me

BMT4me (Figure 1) is a digital health intervention designed to aid in medication management, optimize adherence, and track symptoms or side effects in real time. The app reminds users of medication doses, records the time medication is taken, and asks reasons for missed doses through pop-up notifications. Medications can be typed in the app by the user or entered using an image-to-text option, which converts the medication label into text. As symptom severity can affect adherence and inform the need for medical intervention, it is illustrated by both corresponding emojis and numbers on a 1-to-10 scale to aid understanding and for convenient entry. Additional features include a notes page for recording any details of care to communicate with the provider and the ability to upload pictures. The app can be downloaded to both iOS and Android devices. Currently, availability is limited to the English language, and no clinical data is shared with the medical team during the research study.

**Figure 1 figure1:**
[figure not shown]
BMT4me app wireframes.

### Research Aim and Rationale for Mixed Methods Methodology

The overall aim of this mixed methods study is to design and test a theory-driven mHealth app that can virtually assist caregivers of children post HSCT in improving medication adherence, tracking symptoms, and recording pertinent medical information via the journal feature. This app is different from other medication adherence apps available to patients with cancer in several ways: (1) features (eg, reminders, engaging emojis) in the app are designed to support medication adherence by applying BE principles to provide reminders and tailored notifications for caregivers; (2) it is specific to children after an HSCT; and (3) it provides more than medication reminders, with the design encouraging caregivers to engage with the app via symptom tracking and a journal feature that allows uploading of pictures.

## Methods

### Overall Study Design

The larger mixed methods mHealth app development study consists of 3 phases: (1) prototype development, (2) feasibility and usability, and (3) usability and clinical efficacy (Figure 2). This protocol corresponds to phase 2, feasibility and usability among 15 caregivers immediately upon discharge from the inpatient unit post HSCT. Inclusion criteria include (1) caregiver of child aged 2 to 18 years undergoing allogeneic transplant, (2) access to a smartphone (Android or iOS), and (3) English speaking. Findings from phase 1 informed phase 2, and thus findings from phase 2 will lead to further refinement prior to phase 3. In phase 3, the smartphone app will be compared to usual care in a pilot randomized controlled trial.

**Figure 2 figure2:**
[figure not shown]
Multiphase mixed methods app design of BMT4me. GVHD: graft vs host disease; HCP: health care practitioner; RCT: randomized controlled trial.

### Ethics Approval

All phases of the study have been approved by the Nationwide Children’s Hospital Institutional Review Board (approval number STUDY00000910).

### Phase 2 Study Design

This is a convergent mixed methods design focused on analysis of quantitative and qualitative data simultaneously collected to obtain feedback on the adherence mHealth app interface, usability, and flow and content of the software. Usability testing is the principal means of determining if the system meets its intended purpose [31]. Purposive sampling will be used to identify caregivers of children across the spectrum of age, sex, and diagnoses of pediatric patients treated with HSCT. Caregivers will be evaluated for engagement and understanding of the app in the following steps (Figure 3):

**Figure 3 figure3:**

A stepped approach to usability testing with caregivers.

*Step 1. Unobtrusive observation to measure the intuitiveness of the interface (10-15 minutes).* Initially, caregivers will be briefly introduced to the program and asked to start interacting with the adherence mHealth app. The design team will not intervene or provide instructions and will observe and record participants’ progress.*Step 2. Interactive observation (10-15 minutes).* The design team will begin to interrupt individual participants during the interaction by posing questions regarding observed cues that imply success or delay in program use. Caregivers will be encouraged to verbalize their criticisms of the mHealth app. Since discussion will be based on evolving patterns of interaction, pre-prescribed questions are not possible.*Step 3. Debriefing (15-20 minutes).* Caregivers will be asked to reflect on their experience with the app and its interface and contents, and to indicate their opinions regarding the strengths and weaknesses of the app. These evaluations will be used to establish criteria for refining the content and interactive app features for future development.*Step 4. Passive use observation.* Caregivers will be asked to continue using the mHealth app on their own device until day 100 post HSCT or weaning of the immunosuppressant, whichever occurs first. Passive data modules will be added to the app to capture phone activity (screen on and off times) and will log the participants’ use of the app (eg, time, date, duration of use). Changes in app use and phone activity will be descriptively analyzed and plotted. Subjective measures and standard-of-care immunosuppression serum assays will be recorded weekly. Such passive observational effort of app use and adherence, with a mixed method approach, will be one of the first to be reported in an HSCT population.

At the conclusion, caregivers will complete a 15-minute semistructured interview related to participation in the intervention, as well as the System Usability Scale [32]. Open-ended feedback related to suggestions for further app development will undergo qualitative analysis.

### Data Collection

Trained research assistants will recruit and onboard eligible participants. The participants will sign written consent forms. The research assistant will then conduct one-on-one audio-recorded sessions, which will include a facilitator and a note taker. A project scientist may also participate. The measures listed below will be collected either electronically or in paper-and-pencil form from each caregiver. All participants will receive US $25 at enrollment and US $25 at the conclusion of the study after the exit interview and measures are complete.

#### The BMT4me App

The BMT4me app will collect daily data on medication-taking (taken or not taken), the time medication was taken, barriers or reasons for missed doses, symptoms, and any notes the caregiver completes. Passive use data on phone activity and app use will be collected.

#### Demographic Data Form

The caregiver will report on basic background characteristics, including parent and child age, sex, race, ethnicity, education level, and family income.

#### Medication Adherence Measure

The Medication Adherence Measure (MAM) is a semistructured interview specific to pediatrics, conducted with the parent, to obtain an individual score in each module. The score is represented as percentages of the number of required doses. A total summary score can be calculated across all medications as well separately. This allows for quantification of the degree of adherence on a continuum. MAM has demonstrated adequate convergent validity with MEMS (medication event monitoring system) Caps (*r*=−0.40, *P*<.05) [33]. MEMS Caps are electronic monitors that objectively measure adherence. They contain microelectronic circuits that date and time-stamp each instance the container is opened for a dose of medication. Data from the MEMS Caps will be downloaded using cloud- or computer-based software at each study visit [34,35].

#### System Usability Scale

The System Usability Scale is a 10-item questionnaire routinely used to evaluate the functionality and acceptability of mHealth apps [32,36]. Items are rated on a 5-point scale and scores range from 0 to 100 [36]. Reliability (0.91) and validity (0.81 correlation with a 7-point scale of “user-friendliness”) have been well established [37]. A score of >68% is considered above average [36].

#### Caregiver Satisfaction

Satisfaction will be assessed via semistructured interviews and electronic surveys with caregivers. Caregivers will be asked for feedback regarding participation in the intervention, benefits, burden, barriers, suggested modifications, and overall satisfaction. Suggested modifications to the app and advice to the health care team will also be solicited.

#### Medication Level Variability Index

The medication level variability index is the calculation of the standard deviation of serum assays of immunosuppressants that has been shown to correlate with adherence and clinical outcomes in the solid organ transplant population [38]. Immunosuppressant serum assays are collected weekly during the acute phase. The degree of variation among levels will also be calculated.

### Data Analysis

All interviews will be transcribed verbatim. During qualitative analysis, investigators will use an iterative process of reading, summarizing, and rereading data. The qualitative team is composed of 3 individuals with formal research training in psychology, behavioral health, and nursing. The interview transcripts will be organized and coded using NVIVO software (QSR International). In-vivo coding will occur as new themes emerge from the data. The data will be triangulated by comparing and integrating quantitative survey data with qualitative findings.

Quantitative data will be summarized with descriptive statistics (frequencies, means, and SDs). During the passive use observation period, passive data modules will capture phone activity and caregivers’ application use (eg, time, date, duration of use). Descriptive statistics will be used to analyze phone activity. Correlation analysis will be used to investigate use behavior over time. Acceptability will be assessed by averaging total scores from the System Usability Scale. Consistent with the literature [36], scores >68% on the System Usability Scale will be considered acceptable. The proportion of participants that enroll and complete the study will be examined to assess study feasibility.

The nature of the study is exploratory rather than confirmatory. Thus, the objective of the analysis is effect size estimation, rather than formal hypothesis testing. Threats to power (eg, participant attrition due to patient death, early taper of immunosuppressant medication) are not a primary concern. We will compute pre-post effect sizes (eg, a standardized mean difference) to inform the future randomized controlled trial (phase 3) assessing the efficacy of the intervention.

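### Comparing a bare mean SUS score with 68 in at most 15 caregivers cannot establish above-average usability; report the interval and qualify the verdict

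*Protocol article*

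**What the plan says.** The Data Analysis section sets the rule in two consecutive sentences. The first is "Acceptability will be assessed by averaging total scores from the System Usability Scale". The second, citing the literature, is that "scores >68% on the System Usability Scale will be considered acceptable". The second sentence does not say outright that the mean is what is compared with 68, but the first makes that the natural reading.

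The System Usability Scale section, citing the same reference, gives the meaning of the cut-off: "A score of >68% is considered above average". It also gives the range: "Items are rated on a 5-point scale and scores range from 0 to 100".

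On reporting, the Data Analysis section says "Quantitative data will be summarized with descriptive statistics (frequencies, means, and SDs"). It describes the study as exploratory and says that "the objective of the analysis is effect size estimation, rather than formal hypothesis testing".

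On size, Overall Study Design describes "feasibility and usability among 15 caregivers immediately upon discharge from the inpatient unit post HSCT". Under Phase 2 Study Design, the SUS is completed at the end of participation, so 15 is the largest number of scores the rule can use. Attrition is acknowledged but set aside: "Threats to power (eg, participant attrition due to patient death, early taper of immunosuppressant medication) are not a primary concern".

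**The concern.** The cut-off sits exactly at what the article calls the average benchmark. The quantity compared with it is a mean from a very small sample, and no allowance is made for sampling error. A mean of 69 and a mean of 85 would both be labelled acceptable, although the first says almost nothing about which side of 68 the true mean lies on.

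This matters because 68 is the only numerical criterion in the article. The enrolment and completion proportions used for feasibility carry no threshold. The phase 2 findings are meant to inform refinement of the app before the phase 3 pilot trial, and the article already anticipates high usability scores. A rule that a mildly below-average app often satisfies is a weak check on that expectation.

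**Working it through.** The article gives no power, precision or SD calculation for the SUS, so there is no stated figure to reproduce. The check is how the stated rule behaves.

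**Inputs**
- n = 15 (Overall Study Design), treated as a maximum.
- Cut-off 68 on a 0 to 100 scale (System Usability Scale; Data Analysis).
- SD of SUS totals: not given. Assumed 12.5, 15 and 20 points to show a range.

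**Precision.** Standard error = SD/√15. The 95% half-width is t(0.975, 14) × SD/√15, with t(0.975, 14) = 2.145.

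**Chance that the rule is met.** P(mean > 68 | true mean μ) = 1 − Φ((68 − μ)/(SD/√15)).

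| Assumed SD | Standard error | 95% half-width | P(pass), μ = 66 | P(pass), μ = 64 | Observed mean at which the lower limit reaches 68 |
|---|---|---|---|---|---|
| 12.5 | 3.23 | 6.9 | 0.27 | 0.11 | 74.9 |
| 15 | 3.87 | 8.3 | 0.30 | 0.15 | 76.3 |
| 20 | 5.16 | 11.1 | 0.35 | 0.22 | 79.1 |

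For example, at SD 15 and μ = 66, (68 − 66)/3.87 = 0.516 and 1 − Φ(0.516) = 0.30. The last column is 68 plus the half-width.

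**What a pass near the boundary means.** Take an observed mean of 69, which the rule calls acceptable. At SD 15 the interval is 69 ± 8.3, or 60.7 to 77.3. At SD 12.5 it is 62.1 to 75.9, and at SD 20 it is 57.9 to 80.1. Each includes a wide band of below-average values.

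**Fewer completers.** With 10 scores, chosen only for illustration, the half-width is 8.9 points at SD 12.5 and 14.3 at SD 20.

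**The case against.** **An interval is ordinary analysis-plan content.** The article condenses a fuller document, and an unseen plan may well attach an interval to the mean. The mean, SD and n are also all a reader needs to compute one. This stands, so the absence of an interval is not in itself the finding. The finding is the published verdict rule, which would still turn a point estimate at the average benchmark into a label whatever the plan adds.

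**The estimation aim may not cover the SUS.** The estimation that the article spells out is of pre-post effect sizes, and the SUS is measured only at the end. This is fair, but the aim is stated for the analysis generally, and an interval serves it better than a cut on a mean.

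**The rule does discriminate.** By symmetry with the figures at 64, an app with a true mean of 72 passes 78% to 89% of the time. This stands. Discrimination is imperfect, not absent.

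**Average usability may be acceptable.** Nothing in the article says that it is not. A reader might infer that the two sections contradict each other, but above average and acceptable can both be true of a score over 68. What the data cannot do is show that a mean just over 68 reflects above-average usability.

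**The study is openly exploratory.** It disclaims formal testing, triangulates scores with interviews, and lists its small sample as a limitation. This limits how much weight the point should carry.

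**Conclusion.** The point holds as a modest, inexpensive improvement. With at most 15 scores and an assumed SD of 12.5 to 20, the mean SUS is known to about ±6.9 to ±11.1 points. Apps with true means of 66 and 64 would be called acceptable 27% to 35% and 11% to 22% of the time. These figures depend on the assumed SD and on a normal approximation for the mean. Fewer completers would widen the interval.

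Several stronger readings are tempting, but the article does not support them:
- **That a small sample is why an exactly average app passes half the time.** Any cut-off on a mean is passed about half the time when the true mean equals it, at any sample size. The 15 determines the interval width and how often below-average apps pass.
- **That the SUS result is a gate to phase 3.** The article says only that phase 2 findings inform refinement and later testing.
- **That the scores above 70 reported to date are within noise.** That sentence may describe individual scores, each over 70, which cannot be judged against an interval for a mean. The number of SUS scores behind it is not given.

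**What to change.** In the Data Analysis section:
- Report the mean SUS with a t-based 95% confidence interval, and the number of caregivers scoring above 68 with an exact 95% interval.
- Describe 68 as the average benchmark, in line with the System Usability Scale section.
- Where the interval for the mean includes 68, state that the data are also compatible with below-average usability, in place of an unqualified acceptable verdict.

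The interval should guide the wording and should not become a formal pass/fail test. The study disclaims testing, and a mandatory lower limit above 68 would be demanding: with 15 scores, an app with a true mean of 80 would miss it 18% of the time at SD 15 and 42% at SD 20. Nor is there a case for moving acceptability to the satisfaction survey. The article describes the SUS as a measure of acceptability and gives no scoring for the survey.

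The change needs no new data, visits or participants. Its cost is a less favourable usability statement unless the observed mean reaches about 75 (SD 12.5) to 79 (SD 20) or higher.

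### The planned pre-post standardized mean difference cannot serve phase 3 as an effect size for the app, because phase 2 has no app-free outpatient baseline and no control group

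*Protocol article*

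**What the plan says.** The Data Analysis section sets the aim of the quantitative work: "Thus, the objective of the analysis is effect size estimation, rather than formal hypothesis testing". It then gives the figure and its use: "We will compute pre-post effect sizes (eg, a standardized mean difference) to inform the future randomized controlled trial (phase 3". That later trial is described there as the one assessing efficacy. The section names neither the outcome nor the time point that counts as the starting value.

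Overall Study Design describes this phase as "feasibility and usability among 15 caregivers immediately upon discharge from the inpatient unit post HSCT". No comparison group is described; usual care enters only in phase 3.

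The four steps under Phase 2 Study Design (text at Figure 3) begin with app use: "Initially, caregivers will be briefly introduced to the program and asked to start interacting with the adherence mHealth app". Step 4 continues it: "Caregivers will be asked to continue using the mHealth app on their own device until day 100 post HSCT", or until the immunosuppressant is weaned if that is sooner. Within Step 4, so after app use has begun, the article adds: "Subjective measures and standard-of-care immunosuppression serum assays will be recorded weekly".

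On the course to expect without the app, the Background says: "Studies in children with HSCT report suboptimal adherence rates (52%-78%) that worsen over time".

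**The concern.** A change from before to after informs an efficacy comparison only if the starting value reflects the same setting without the app, and if little else would have changed meanwhile. The schedule as described meets neither condition. It leaves no outpatient time before the app, and the Background gives a reason to expect change regardless.

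At stake is what phase 2 hands to phase 3. Phase 3 compares the app with usual care between groups. A within-group change labelled as an effect size invites readers to treat it as a preliminary estimate of that comparison. A helpful app could show a negative figure, and an inert one a figure well away from zero.

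**Working it through.** The article gives no effect size, SD, alpha or power, and does not derive the 15, so there is no stated figure to reproduce. The check has three parts.

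**1. What the starting value can be.** Setting the quoted sections side by side leaves two options.

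- *A value from before discharge.* The variability index section says "Immunosuppressant serum assays are collected weekly during the acute phase", and the Background counts the acute phase as the first 100 days after transplant, so inpatient levels could be used. (A later paragraph of the Introduction counts it from discharge.) An adherence interview at enrolment would likewise look back on time before discharge. Either value precedes caregiver-managed dosing after discharge.
- *An early value after discharge.* The app is already in use, so this is not a value without the app.

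**2. What the difference then estimates.** Let U(t) be the expected outcome at time t without the app and A(t) the app's effect against usual care at that time, both in SD units. Phase 3 is after A(post).

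- Pre-discharge start: post minus pre = [U(post) - U(pre)] + A(post). The first bracket holds the time trend and the change of setting.
- First outpatient week as start: post minus pre = [U(post) - U(1)] + [A(post) - A(1)]. If the app's effect is constant, the second bracket is zero and only the trend remains.

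Illustration with an assumed constant app effect of 0.3 SD; the trends are also assumed, since the article gives no rate of decline and no SD:

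| Change without the app (SD) | Pre-discharge start | App-exposed start | Target A(post) |
|---|---|---|---|
| -0.5 | -0.5 + 0.3 = -0.2 | -0.5 | 0.3 |
| 0 | 0.3 | 0 | 0.3 |
| +0.2 | 0.2 + 0.3 = 0.5 | +0.2 | 0.3 |

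Only a pre-discharge start with no net change from trend or setting recovers the target. The Background points to the downward rows for adherence. The upward row covers other possibilities, such as caregivers settling into a home routine, which is an assumption.

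**3. Precision.** Assume the mean change is divided by the SD of change, so that SE = sqrt(1/n + d²/(2n)). Take an observed d of 0.5, chosen for illustration.

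- n = 15 (every caregiver has both values): SE = sqrt(1/15 + 0.25/30) = sqrt(0.0750) = 0.274. The 95% interval is 0.5 ± 1.96 × 0.274 = -0.04 to 1.04. The exact noncentral-t interval is -0.05 to 1.03.
- n = 12 (an assumed three incomplete): SE = sqrt(1/12 + 0.25/24) = sqrt(0.09375) = 0.306. The interval is -0.10 to 1.10.

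**The case against.** - **The source is a condensed article.** The full protocol may define the outcome and the starting value, and their absence here is not a fault. That stands. It does not remove the problem: if caregivers start the app at discharge, no baseline form can create outpatient time without it. The difficulty lies between elements that the article does state.
- **The study is exploratory, and the small sample is acknowledged.** Both are true, in Data Analysis and in the Discussion. Imprecision alone would not be a finding in a usability study. But an exploratory aim excuses the absence of hypothesis tests, not the reading of a confounded change as an effect size. The limitations listed (one site, few caregivers, English only) do not mention this one.
- **The article never says the figure is the app's effect against usual care.** Correct. It says only that the figure will inform the phase 3 trial; the fault is in that use.

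A reader might infer that phase 3 will be mis-sized or wrongly abandoned. The article does not support this: it states no sample size calculation and no go/no-go rule for phase 3, which it calls a pilot. A reader might also take the quoted adherence range as a 26-point fall (78 - 52); it is a range of reported rates, not a measured decline. Nor can one say that the figure will be inflated by its choice of SD, because the article does not say which SD will be used.

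**Conclusion.** The point holds in a limited form. As described, the pre-post standardized mean difference cannot be read as the app's effect against usual care, and the bias could go either way. Its size cannot be fixed from the article, and the table above only shows what assumed trends would do. With 15 pairs, an observed 0.5 is compatible with anything from about zero to about 1.04.

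The conclusion rests on app use starting at discharge as described, and on phase 3 comparing the app with usual care. It leaves the phase 2 usability and feasibility aims untouched: the System Usability Scale scores, enrolment and completion do not depend on this figure. The text should be corrected, but the point does not call the study into question.

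**What to change.** In Data Analysis, replace the sentence on pre-post effect sizes so that the pre-post standardized mean difference is not an effect size input to phase 3. State instead that phase 2 will pass on:

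- the outpatient adherence level and its between-caregiver SD, each with a 95% confidence interval (an SD from 15 caregivers is itself imprecise);
- the extent of missing data;
- the proportion completing.

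Base phase 3 on a justified between-arm difference against usual care.

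If within-person change is still reported, name the outcome, take the first outpatient week as reference, give a 95% confidence interval, and label it as change while using the app that is not attributable to the app. A first-week reference suits an adherence percentage. It does not suit the variability index, because weekly assays give about one level in that week and an SD needs several; that index is better summarised over the outpatient period.

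The change is one of wording and needs no new data. The cost is that phase 2 then offers no preliminary efficacy figure.
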